## Abstract

**Background:**

Tuberculosis (TB) in children is one of the most significant public health crises in Somalia. This issue is aggravated by the fact that only 36.7% of children aged 12 to 23 months receive the Bacillus Calmette–Guérin (BCG) vaccine in Somalia, which helps prevent TB-disseminated diseases. Among the major factors that contribute to poor BCG uptake and TB prevention practices are the lack of maternal knowledge, negative attitude, and poor self-efficacy toward the BCG vaccine and TB prevention practices. As such, pregnant women play a vital role in ensuring timely, routine BCG vaccination for their newborns and adherence to TB prevention practices.

**Objective:**

This study aims to develop, implement, and evaluate the impact of health education intervention using the information-motivation-behavioral (IMB) skills model to improve knowledge, attitudes, and self-efficacy regarding BCG uptake and TB prevention among pregnant women in Banadir Hospital.

**Methods:**

This single-blind randomized controlled trial enrolled a sample of 370 pregnant women recruited at Banadir Hospital in Mogadishu, Somalia. Eligible participants will be randomized to an intervention group receiving an IMB-based health education and to a waiting list control group, in a 1:1 ratio. Outcome assessments will be conducted at baseline, 2-month follow-up, and 4-month follow-up. The primary outcomes are BCG vaccine uptake and TB prevention practices. Secondary outcomes include knowledge, attitudes, and self-efficacy related to the BCG vaccine and TB prevention practices. The IMB-based health education intervention program consists of 6 sessions, with 1 group per session, and with each session containing 30 participants. The effects of the intervention will be assessed by handing out the same self-administered questionnaires at baseline, 2-month postintervention, and 4-month postintervention.

**Results:**

A total of 370 pregnant women were recruited at baseline in November 2021, with 185 assigned to the intervention group and 185 assigned to the control group. In January 2022, the 185 pregnant women enrolled in the intervention program and completed the sessions by February 2022. Data collection for the 2-month and 4-month postintervention assessments was completed in June 2022. The findings of this study will be reported by the beginning of 2026.

**Conclusions:**

The developed health education intervention module in this study has the potential to be adopted and included as part of routine antenatal care services. Its implementation could effectively raise awareness among pregnant women in Somalia regarding the importance of BCG vaccination and TB prevention practices, ultimately mitigating childhood mortality rates associated with TB-disseminated diseases in the country.

## Introduction

Tuberculosis (TB) remains a prevalent health issue worldwide, with over 10 million new cases annually [1]. TB cases are also reported in children younger than 15 years and are referred to as childhood TB. Moreover, children younger than 5 years are particularly vulnerable to developing active TB disease [2]. In 2011, the World Health Organization reported its first estimate of annual global childhood TB, which amounted to 490,000 cases [3]. In 2022, approximately 1.25 million children and young adolescents were diagnosed with TB, with 47% of these cases occurring in children younger than 5 years. This age group represents 12% of the overall TB incidence of 10.6 million [4]. However, approximately 51% of these cases were either undiagnosed or not reported to national TB programs. The gap is even more pronounced among children younger than 5 years, with 58% of estimated cases being missed, compared to 30% for individuals aged 15 years and older [3].

The risk factors contributing to the development of TB disease among children have received increasing attention over the years. Contact with known adult TB cases is a significant risk factor for both children and adults [5,6]. A study conducted in Guinea-Bissau found that children younger than five years living in the same household as an adult with TB faced a markedly higher risk of death, with the risk being up to 8 times higher for those whose mothers were affected by the disease [7]. Other important risk factors include lack of BCG vaccination, severe malnutrition, and knowledge and attitude toward TB [8-10].

Somalia is classified as one of the least developed countries and faces a significant burden of TB, particularly multidrug-resistant TB [11]. In 2023, the TB incidence in Somalia was reported at 246 cases per 100,000 population [12]. Despite the heightened vulnerability of children due to malnutrition and limited access to health care, only about 56.4% of TB cases are detected, resulting in many children going without the necessary treatment [13]. Furthermore, according to the Somali National Strategic Plan 2020‐2024 for Tuberculosis, 22% of TB cases occur in children younger than 15 years [14].

Somalia, as a TB-endemic country, faces significant challenges, particularly low BCG vaccine uptake, limited knowledge of childhood TB, and negative attitudes toward the disease. According to the Somali Health Demographic Survey conducted in 2020, only 36.7% of children aged 12 to 23 months received the BCG vaccine, marking one of the lowest coverage rates in Africa [15]. Similarly, community-based studies in Somalia revealed that only 4.7% of participants correctly identified bacteria as the cause of TB, while just 44.7% of participants were aware of the importance of covering their nose and mouth when coughing and sneezing to prevent TB transmission [16,17]

Previous intervention studies have demonstrated the positive impact of health education on improving BCG uptake and TB prevention practices [18,19]. Similarly, health theories are important for understanding health behaviors, designing effective interventions, and evaluating program success. This study suggests using the information-motivation-behavioral (IMB) skills model construct over theories such as the health belief model and the theory of planned behavior, which predominantly center on perceptions and beliefs concerning health threats but may underestimate the crucial motivational aspect in behavior change. The IMB skills model emphasizes 3 essential constructs for promoting behavior change: providing relevant information regarding the desired behavior (which alone is insufficient for behavior change), fostering appropriate motivation to engage in the desired behaviors, and ensuring that individuals possess the necessary skills and competencies to effectively perform the desired behaviors [20].

However, no studies were identified during the literature search that assessed health education interventions specifically related to a model concerning BCG vaccination and TB prevention in Somalia. Therefore, this study proposes to develop, implement, and assess the effects of an IMB-based health education intervention on BCG uptake and TB prevention practices among pregnant women attending the antenatal care (ANC) clinic at Banadir Maternal and Child Hospital, Mogadishu, Somalia.

## Methods

### Study Location

This study selected Banadir Maternal and Child Hospital, which is a public referral hospital, as the study location. This hospital is located in Mogadishu, the capital city of Somalia. Also known as Xamar, it is the most populous city in Somalia, with an estimated 2 million residents [21], and stretches along the southern coast of Somalia on the Horn of Africa. This particular hospital was chosen due to its strategic geographical location at the center of the city and its considerable size and high patient load, making it one of the largest hospitals in the area. The hospital comprises 2 main departments: maternity and pediatrics. Under the Maternity Department, the hospital operates an ANC clinic from Saturday to Thursday, providing support to expectant mothers throughout their pregnancy. Other essential services that are available at this hospital include the Diarrhea Treatment Center, Blood Transfusion Unit, Emergency Unit, TB Center, and Research and Training Center.

### Study Design

A single-blind randomized controlled trial will be conducted in this study, with only the participants blinded to their assigned group. The participants will be randomly categorized into the intervention group and control group. The study protocol will be reported in accordance with the Standard Protocol Items: Recommendations for Intervention Trial (SPIRIT) 2013 Guideline [22] (Figure S1, Multimedia Appendix 1).

### Study Duration

Planning of the study protocol began in January 2021, and data collection was completed in June 2022.

### Study Population and Study Setting

The study population consists of pregnant women attending the Banadir Maternal and Child Hospital, Mogadishu, for ANC visits. The inclusion criteria include mothers with a gestational age range of 25 to 33 weeks, plans for postnatal follow-up at the hospital, and residence in Mogadishu, including internally displaced persons. The exclusion criteria include mothers who visited the hospital for other health conditions, those of non-Somali nationality, and those who had previous health education training related to immunization and TB prevention practices.

### Sample Size

The 2-sample mean formula was used to determine the sample size for this study. This formula considers the mean and SD of TB preventive practices from a previous health education program conducted by John [19], where a SD of 4.40, an intervention group mean of 20.71, and a control group mean of 18.45 were used in the calculation. To ensure adequate statistical power, several adjustments were made for the estimated eligibility (90%) and attrition rate (30%), with a 95% significance level and 80% desired power. The anticipated high attrition rate is primarily due to the impact of the COVID-19 pandemic, which created significant barriers to participation in the study. Based on this formulation, the total sample size for this study was 370 participants, with an equal number of participants in both the intervention and control groups.

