### Data Analysis

Collected data were entered into SPSS software (version 27.0; IBM Corp) before proceeding with data cleaning procedures. Both statistical and graphical normality tests were applied to continuous variables, such as age, knowledge, attitude, and self-efficacy. At baseline, the comparison of variables between groups used appropriate statistical measures based on the distribution of data. For normally distributed data, results are reported as mean (SD), and comparisons were conducted using an independent *t* test. For non-normally distributed data, results were reported as median (IQR), and comparisons were conducted using the chi-square test and the Mann-Whitney *U* test.

To evaluate the main effect of the IMB-based intervention modules on the response variables over time, as well as the group-time interactions, repeated-measures ANOVA was used for normally distributed data. For non-normally distributed data, generalized linear mixed models were applied to account for individual-level variability among participants, or generalized estimating equations were used when focusing on overall population-level trends. Intention-to-treat analyses were conducted separately for the intervention and control groups, and missing data were addressed using multiple imputations. Results were reported as differences between groups with 95% CIs. Statistical significance in this study was set at α=.05.

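### The total of 370 does not follow from the stated sample-size inputs, which give about 190; the derivation and the power statement need correcting, not the enrolment

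*Protocol article*

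**What the plan says.** The Sample Size section names the method: "The 2-sample mean formula was used to determine the sample size for this study". It takes its values from an earlier health education programme: "a SD of 4.40, an intervention group mean of 20.71, and a control group mean of 18.45 were used in the calculation". It then says that "several adjustments were made for the estimated eligibility (90%) and attrition rate (30%), with a 95% significance level and 80% desired power". The conclusion is presented as the output of these inputs: "Based on this formulation, the total sample size for this study was 370 participants", split equally between the groups. The Results paragraph of the Abstract confirms that the total counts randomised women, "with 185 assigned to the intervention group and 185 assigned to the control group".

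The Data Analysis section fixes the error rate: "Statistical significance in this study was set at α=.05". Neither section says whether the test is one-sided or two-sided. The Sample Size section mentions no design effect, multiplicity adjustment or calculation for a second outcome.

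**The concern.** The section gives a complete set of inputs and an answer, and the two disagree by a factor of almost two. This is more than abbreviation in a journal article. If a further factor was applied in a fuller document, the statement that 370 follows from this formulation would still be wrong, because that formulation leaves out a near-doubling.

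The results are still to be published. Readers will judge a small or null difference in practice scores against 80% power for 2.26 points, which misstates what 370 women can detect on the plan's own assumptions. About twice as many women were enrolled as the stated justification requires, so the number lacks its stated rationale.

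Two smaller faults sit in the same sentence. A significance level of 95% confuses confidence with significance. The 90% eligibility factor is applied to the wrong count: under Recruitment, women are checked against the criteria before entry, and under Data Collection, random assignment follows the baseline questionnaire. The 370 randomised women were therefore already eligible.

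**Working it through.** **Inputs** (Sample Size, except alpha, which is from Data Analysis): difference 20.71 − 18.45 = 2.26; SD 4.40; standardised difference 2.26/4.40 = 0.514; alpha .05, two-sided assumed; power 80%; eligibility 90%; attrition 30%; allocation 1:1.

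**Attempt to reproduce 370**

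- Evaluable per group: n = 2(1.960 + 0.842)² × 4.40² / 2.26² = 59.5, so 60. The t-based solution is 60.5, so 61.
- Both adjustments (0.90 × 0.70 = 0.63): 59.5/0.63 = 94.4; 60/0.63 = 95.2; 61/0.63 = 96.8. That is 95 to 97 per group, or 190 to 194 in total.
- Attrition only: 60/0.70 = 85.7, so 86 per group and 172 in total; t-based 60.5/0.70 = 86.4, so 87 and 174.
- Stated: 185 per group, 370 in total. Ratio: 185/95.2 = 1.94 to 185/94.4 = 1.96.

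**Other conventions at the stated alpha and power** (totals)

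| Convention | Total |
|---|---|
| One-sided, both divisors | 150 |
| One-sided, attrition only | 136 |
| Multiply by 1.3 and 1.1 | 172 |
| Add 40% | 168 |
| Divide by 0.6 | 200 |

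None approaches 370. Changing the inputs, with both divisors kept, gives 254 at 90% power, 316 at 95% power and 284 at alpha 0.01 with 80% power. Only alpha 0.01 with 90% power comes near (360), and it contradicts the text.

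**What 370 provides for the practice score**

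- After 30% attrition: 185 × 0.70 = 129.5, so 129 per group. SE = 4.40 × √(2/129) = 0.548. Two-sample t power for 2.26 is 98.4%.
- Difference detectable at 80% power: (1.960 + 0.842) × 0.548 = 1.53; t-based 1.54.
- With both factors counted as losses: 185 × 0.63 = 116.6, so 116 per group, power 97.4%.

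**How far that power depends on its conditions** (129 per group, normal approximation)

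- *Clustering.* Intervention Structure and Delivery says the intervention arm was taught in six groups of 30 to 35. At 129 evaluable women that is 129/6 = 21.5 per group, with no such grouping in controls. Variance of the difference = (4.40²/129) × [1 + (1 + 20.5 × ICC)]. The documents give no ICC; for assumed values, power is 98% at 0, 96% at 0.02, 92% at 0.05 and 83% at 0.10. At 0.10 the detectable difference rises to 2.18. Allowing for the few clusters would lower power further.
- *Change scores.* Table 2 defines the outcome as a change in total practice score; Sample Size does not say what kind of score 4.40 belongs to. If it is the SD at a single time, the SD of change is 4.40 × √(2(1 − ρ)). Power is then 83% at ρ = 0, 94% at 0.3 and 98% at 0.5, where ρ is an assumed correlation.

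**The case against.** The strongest reply is that nothing in the trial is endangered. The error runs toward more women, 80% is only the desired power, and enrolment and follow-up are complete. No participant number or analysis changes. That stands, and it limits the severity. It does not make the stated derivation right.

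A second reply is that printing 98% power would replace one unsupported figure with another. This also stands in part: the figure needs independent observations and an SD of 4.40 for the analysed score, and the documents establish neither. It may be reported only with those conditions.

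Three stronger readings are tempting and are not supported:

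- *That the two-group total was mistaken for a per-group number and doubled again.* Four times 59.5, divided by 0.63, is 378, and with 60 it is 381. These are near 370 but do not equal it, and the document says nothing of the kind. It is an inference.
- *That 370 has a known adequacy, or inadequacy, for BCG uptake.* The detectable difference depends on an assumed control uptake. With 129 per group it is about 17 percentage points at 36.7% to 50%, about 14.6 at 70% and about 12 at 80%. The 36.7% is a national survey figure for children aged 12 to 23 months, whereas the trial enrols antenatal attenders who plan postnatal follow-up at the hospital. The absence of a BCG calculation from a condensed article is not part of this arithmetic error.
- *That the trial certainly has 98% power.* As shown, clustering or a change-score analysis could bring it close to 80%.

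**Conclusion.** The point holds as a reporting error of moderate severity. On the stated inputs the total is about 190 with both adjustments, or about 172 to 174 with attrition alone. The stated 370 is about 1.95 times the larger of these. The result assumes a two-sided 5% test, but a one-sided test moves further from 370, so the conclusion does not depend on that choice.

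The 80% figure is the power of the smaller design. For 370 randomised and 30% lost, power for 2.26 points is about 98%, and 80% power corresponds to about 1.54 points, under independence and with 4.40 as the SD of the analysed score. The source of the extra factor is unknown.

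**What to change.** Change the Sample Size text only; enrolment stays at 370.

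1. Either correct the derivation to about 190 and say that 370 were enrolled, or state and justify the additional factor of about 1.95 that led to 370.
2. Replace the 95% significance level with a 5% significance level and state its sidedness.
3. Apply the 90% eligibility factor to the number screened. The number to randomise then rests on attrition alone (about 172 to 174 on the stated inputs).
4. State the power that 370 provides with its conditions: about 98% for 2.26 points, or 80% for about 1.54 points, at 129 per group after 30% attrition, if observations are independent and 4.40 is the SD of the analysed score. Say which score 4.40 describes. Add that power is lower if outcomes cluster within the six education groups, for example about 92% at an assumed ICC of 0.05 and 83% at 0.10.

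Do not give a cause for the discrepancy unless the authors can confirm it from their records, and do not add a BCG detectable difference without its assumed control uptake. The cost is a few sentences, with no new data and no change to the analysis.

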### Recruitment

Potential participants were recruited over a 4-week period from the ANC clinic at Banadir Maternal and Child Hospital. To ensure an organized and systematic selection, their names were sorted into the ANC electronic register in chronological order. After obtaining informed consent from all participants who agreed to take part in the study, their eligibility was assessed by applying the inclusion and exclusion criteria checklist. The recruitment process is summarized in Figure S2 (Multimedia Appendix 1).

### Randomization, Allocation Concealment, and Blinding

Randomization was performed at the individual level, with pregnant women as the sampling unit. Ensuring an equal allocation ratio (1:1), participants were randomly assigned into the intervention group, which received the IMB-based health education intervention, or the control group, which was placed on a waiting list. The randomization process was conducted using computer-generated random numbers using a web-based calculator (GraphPad; GraphPad Software) by hospital staff who were independent of all other research processes. The generated sequences were placed in sealed opaque envelopes. Subsequently, another hospital staff member, who was also independent of the research team, was responsible for opening the envelopes sequentially and assigning participants to either the intervention or control group.

### Intervention

#### Intervention Development and Validation

The intervention modules were developed based on relevant sources from the World Health Organization, the Ministry of Health of Somalia [23], and publications and guidelines from previous studies [24]. As presented in Table 1, the IMB components, namely information, motivation, and behavior skills, were used to develop the intervention program. Each module’s content was examined by a panel of experts consisting of 6 public health specialists and pediatricians from Universiti Putra Malaysia, the Ministry of Health of Somalia, and Bandir Hospital. To ensure effective delivery of the module content to participants, 2 female intern students provided a single, intensive training session lasting approximately 3 hours. To further prepare the interns, a follow-up session was scheduled a day before the intervention sessions began. Both interns had backgrounds in medicine and have demonstrated competency in Somali communication, which enhanced their ability to engage effectively with participants.

**Table 1. T1:** Summary of intervention program content and delivery.

Theory construct module	Health education content	Delivery strategy	Estimated duration
Module 1: information	Basic knowledge of childhood TB^a^, including cause, transmission, signs and symptoms, severity, and complications.	Lecture using PowerPoint presentation, question-and-answer sessions.	30 min
Module 2: information	Benefits, schedule, and side effects of the BCG^b^ vaccine; respiratory hygiene (cough etiquette); and environmental control measures.	Lectures using PowerPoint presentations, question-and-answer sessions.	30 min
Module 3: motivation	Importance of the BCG vaccine, respiratory hygiene (cough etiquette), and environmental control measures; religious and cultural leaders addressing the benefits, safety, and halal status of the BCG vaccine, and normalizing face mask use.	Interactive discussion, brainstorming sessions, video presentations, and lectures.	1 h
Module 4: behaviorSkills	Self-efficacy evaluation related to receiving the BCG vaccine and childhood TB prevention practices; problem-solving focused on challenges and solutions; reinforcement through a 1-month follow-up call for mothers in the intervention group to reinforce key intervention points and prioritize the administration of the BCG vaccine for their newborns.	Role play (video), interactive session, brainstorming exercise, and a 1-month follow-up call to reinforce.	1 h and 30 min

a TB: tuberculosis.

b BCG: Bacillus Calmette–Guérin.

Pretesting of the questionnaire was conducted among 36 pregnant women in Banadir Hospital who were not part of the study to assess the reliability of the questionnaire. Reliability was carried out using Cronbach α to assess for internal consistency. The Cronbach α coefficients for knowledge, attitudes, and prevention practices were 0.774, 0.829, and 0.689, respectively. The results were within the acceptable range of 0.60 to 0.95 [25].

